### Sample size

Based on results of meta-analyses [1,17,18], we can expect interventions for caregiving relatives of people with dementia to have small to medium effects on the mental and physical health of caregivers (*d*=0.14 to 0.41). Results from the previous project [4] similarly indicate that this telephone-based intervention has small to medium effects (*f*=0.18 to 0.29).

Hypothesizing a small effect size in a two-group design with three measurement points, an *α* of.05, a power (1−*β*) of.80, and a *ρ* of.50, we need a sample of *n*=82 per group [19]. Therefore, we aim to have 164 participants in the randomized groups. Assuming a dropout rate of 30%, we plan to recruit 118 persons in each randomized group. Additionally, we aim to recruit as many people for the F2F group as possible (with *n*=118 as cut-off criterion).

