### Data analysis

The data will be analyzed with SPSS version 22.0 (IBM Corp., Armonk, NY) and MPlus version 7.0 (Muthén & Muthén, Los Angeles, CA). Data cleaning and analyses will be performed using SPSS/Mplus syntax operations. Possible baseline differences between trial arms will be statistically tested and further analyses will be adjusted for imbalances in the baseline scores. The primary analysis will be by intention to treat. For the primary outcomes, analyses will be corrected for multiple testing.

As sensitivity analyses, completers of all assessments will be analyzed separately. Hypotheses tests will be performed at *α*=.05. The numeric outcomes will be analyzed using analyses of variance; categorical outcomes will be analyzed using *χ*^2^-tests. Additionally, latent change model analyses will be performed for continuous longitudinal outcome data. To handle missing data, full information maximum likelihood estimation will be conducted in MPlus. As part of the questionnaire adaptation, factor, reliability, and correlation analyses will be performed.

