## Discussion

This study will evaluate whether TEL improves depressiveness, burden of care, health complaints, and problem-solving ability compared to usual care and assess whether TEL is as effective as F2F. One strength of this study is its robust design and follow-up assessment allowing evaluation of the long-term effects of TEL. For the first time, it will be possible to test intervention effects of TEL in established care services.

However, there will also be several challenges in this study. In particular, enrolling a sufficiently large sample in the F2F group will be a major difficulty, which we hope to overcome by recruiting via different media and by directly assigning participants to F2F.

The F2F sample will be especially selective, as it will consist of an exclusively urban and mobile population. Since possible F2F participants will be selected from the overall recruited sample, the remaining subsample being randomized will potentially be more rural and less mobile than the original sample recruited.

To ensure adequate and homogeneous application of therapeutic strategies, extensive training prior to implementation, application through CBT-qualified therapists, regular supervision (4 to 6 times per year) and documentation of the implementation will be essential strategies. To determine treatment integrity, independent CBT-qualified therapists will assess psychotherapeutic competence and adherence in randomly selected audio and video recordings of the sessions.

In case the intervention is terminated prematurely, an attempt will be made to continuously include the participant in the data collection. To avoid selective dropout in the control group, this group will receive an incentive. Blinding is not possible in the design of the proposed study, since both the family caregivers and the therapists will know whether a therapy is conducted. To nevertheless guarantee an independent assessment of intervention efficacy, the data collection will be performed by researchers who are not involved in the therapy.

In summary, this will be the first study to test the implementation of telephone-based cognitive-behavioral therapy in established care provision structures in a randomized controlled trial. If TEL proves to be effective in improving primary outcomes, our results will be relevant to practice. Hence, TEL could be used on a large scale. Thus, the results of the study will be used to improve support services for family-caregivers.

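### The completer analysis named as the sensitivity analysis cannot show whether a TEL effect survives dropout that is informative and differs between the arms

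*Protocol article*

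**What the plan says.** All statements are in the protocol article.

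- **Primary analysis (Data analysis):** "The primary analysis will be by intention to treat".
- **Methods (Data analysis):** "The numeric outcomes will be analyzed using analyses of variance", followed by "Additionally, latent change model analyses will be performed for continuous longitudinal outcome data".
- **Missing data (Data analysis):** "To handle missing data, full information maximum likelihood estimation will be conducted in MPlus".
- **Sensitivity analysis (Data analysis):** "As sensitivity analyses, completers of all assessments will be analyzed separately". The article names no other.
- **Expected loss (Sample size):** "Assuming a dropout rate of 30%, we plan to recruit 118 persons in each randomized group".
- **Retention (Discussion):** "To avoid selective dropout in the control group, this group will receive an incentive". The same section says that data collection will be attempted for participants who end therapy early, and that blinding is not possible.

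**The concern.** A sensitivity analysis should relax the assumption that is in doubt. FIML is valid if data are missing at random, meaning that dropout depends only on data that were observed and modelled. An analysis of completers generally asks for more: dropout unrelated to outcome, or related only to covariates that are adjusted for. It therefore tightens the assumption. If the ANOVA for numeric outcomes is a repeated-measures analysis with listwise deletion, it already uses only those with all assessments, and the sensitivity analysis is nearly the same analysis again.

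What is at stake is how agreement will be read. If completers and FIML both favour TEL, a reader will take the result as robust to dropout. Yet both can be wrong in the same direction if TEL participants who leave do worse than their observed data predict and controls who leave do not. The design leaves room for this: participants know their allocation and only one arm is paid to stay.

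**Working it through.** **1. The plan's own figures.** 82 / (1 − 0.30) = 117.1, rounded up to 118, as stated. Expected completers per arm are 118 × 0.70 = 82.6, so about 118 − 82.6 = 35 per arm would be lost. The 82 per group also reproduces: a group-by-time interaction with f = 0.10 (the article says only that the effect is small), three time points, ρ = 0.50 and α = 0.05 gives a total of 164 with power 0.805. The sample size is not in question here.

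**2. Size of the bias.** With p the dropout fraction and δ the amount by which dropouts are worse than the missing-at-random prediction (in SD):

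bias in the TEL effect = p_TEL × δ_TEL − p_control × δ_control

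The article gives p = 0.30. Every δ, and the 20% dropout in the third row, is an assumption.

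| p_TEL, δ_TEL | p_control, δ_control | Bias (SD) |
|---|---|---|
| 0.30, 0.2 | 0.30, 0 | 0.06 |
| 0.30, 0.5 | 0.30, 0 | 0.15 |
| 0.30, 0.3 | 0.20, 0.3 | 0.09 − 0.06 = 0.03 |
| 0.30, 0.3 | 0.30, 0.3 | 0 |

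The Sample size section expects d = 0.14 to 0.41, so 0.15 slightly exceeds the lower end and is about a third of the upper end (0.15 / 0.41 = 0.37).

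**3. Would the completer analysis reveal it?** Simulation with 118 per arm, unit SD, correlation 0.5 between time points, 30% dropout per arm, 2,000 replicates and a true effect of zero. Higher scores are worse, so a negative difference is a false benefit of TEL. Where dropout depends on a score, the log-odds of dropout change by 1 per SD (an assumed strength).

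| Dropout mechanism | FIML at T2 | Completers, T2 mean | Completers, change from T0 |
|---|---|---|---|
| Random in both arms | −0.003 | −0.003 | −0.006 |
| TEL: on observed T0; control: random | −0.004 | −0.131 | +0.126 |
| TEL: on observed T1; control: random | −0.003 | −0.127 | +0.001 |
| Both arms: equally on unseen T2 | +0.006 | +0.006 | +0.002 |
| TEL: on unseen T2; control: random | −0.184 | −0.251 | −0.125 |
| Opposite directions on unseen T2 | −0.368 | −0.505 | −0.253 |

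In the last two rows every method shows a false benefit. The gap between FIML and the completer T2 mean is 0.131 − 0.004 = 0.127 in the second row, where FIML is right, but only 0.251 − 0.184 = 0.067 in the fifth, where FIML is wrong. The size of the disagreement does not tell the two situations apart.

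**4. What a tipping-point analysis would show.** Take the upper expected effect, 0.41 SD, with a standard error between 0.13 (√(2/118), no missing data) and 0.15 (about the simulated FIML value). Shift TEL dropouts only and hold the standard error fixed:

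- Significance at two-sided 0.05 is lost at (0.41 − 1.96 × 0.13) / 0.30 = 0.52 SD, or (0.41 − 1.96 × 0.15) / 0.30 = 0.39 SD.
- The effect is null at 0.41 / 0.30 = 1.37 SD.
- If TEL dropouts take the control mean, the effect becomes 0.41 × 0.70 = 0.29 SD.

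The article will correct the primary outcomes for multiple testing. A stricter threshold brings the loss of significance at a smaller shift.

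**The case against.** **This is an omission that an article may leave to the analysis plan.** It is fair that an unseen full protocol or SAP may add analyses. A reader might infer that completers are the trial's only sensitivity analysis, and the article cannot support that. The point rests on the analysis the article does name, which is poorly suited to that role whatever else exists.

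**FIML is not stated to be the primary analysis.** This stands. The text names ANOVA, adds latent change models, and gives FIML as the way missing data are handled. Reading FIML as primary is reasonable but is not the article's wording. Under the other reading, ANOVA on complete cases, the completer analysis checks even less.

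**The completer contrast is not always biased.** Also true. It is unbiased if dropout distorts both arms equally, or depends only on covariates that are adjusted for. The article plans adjustment for baseline imbalances, and adequate baseline adjustment would remove the bias in the T0 row of the table. Comparing completers with FIML has a limited use for dropout related to observed data, but none for dropout related to unseen outcomes.

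**Leaving therapy is not the same as missing data.** This stands and tempers the concern. Follow-up will be attempted after early termination, questionnaires are supported by telephone interview, and the incentive is itself a retention measure. These steps reduce missing data; they do not test the assumption about what remains missing.

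**The shifts are chosen.** They are. No section gives a value for them, which is why a displayed range is needed.

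**Conclusion.** The point holds in a limited form. The named sensitivity analysis generally assumes more about missingness than the FIML handling beside it, and so cannot show whether a TEL versus usual-care effect survives informative dropout that differs between arms. With 30% dropout in TEL, an assumed departure of 0.2 to 0.5 SD in TEL only overstates the effect by 0.06 to 0.15 SD. Equal dropout with equal departure gives a bias of about zero.

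A reader might go further and infer that informative dropout is likely here, or that a positive result would be an artefact. The article supports neither. It assumes the same 30% in each randomized group, reports no dropout pattern, and plans continued follow-up. At the upper end of the expected effect, a one-sided shift of about 0.4 to 0.5 SD would be needed before nominal significance is lost. The weakness lies in the check, and it should be corrected before the data are analysed.

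**What to change.** - Keep the FIML-based intention-to-treat analysis, and say explicitly that it is primary if that is the intention.
- Name as the sensitivity analysis a multiple imputation of missing T1 and T2 outcomes that departs from missing at random. It can be delta-adjusted, with shifts varied separately by arm from 0 to 0.5 SD and beyond until the conclusion changes, or control-based, with TEL dropouts following the usual-care trajectory. The control-based form is one assumption among several, so the delta grid is the more informative display.
- Judge the tipping point at the multiplicity-corrected threshold used for the primary outcomes.
- Report the completer analysis as descriptive only.

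The cost is a change of wording and some programming with standard multiple-imputation software. No new data and no change in sample size are needed. The drawback is that the result depends on a range of assumed shifts, which must be shown and justified rather than reduced to one answer.

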## Discussion

This study will evaluate whether TEL improves depressiveness, burden of care, health complaints, and problem-solving ability compared to usual care and assess whether TEL is as effective as F2F. One strength of this study is its robust design and follow-up assessment allowing evaluation of the long-term effects of TEL. For the first time, it will be possible to test intervention effects of TEL in established care services.

However, there will also be several challenges in this study. In particular, enrolling a sufficiently large sample in the F2F group will be a major difficulty, which we hope to overcome by recruiting via different media and by directly assigning participants to F2F.

The F2F sample will be especially selective, as it will consist of an exclusively urban and mobile population. Since possible F2F participants will be selected from the overall recruited sample, the remaining subsample being randomized will potentially be more rural and less mobile than the original sample recruited.

To ensure adequate and homogeneous application of therapeutic strategies, extensive training prior to implementation, application through CBT-qualified therapists, regular supervision (4 to 6 times per year) and documentation of the implementation will be essential strategies. To determine treatment integrity, independent CBT-qualified therapists will assess psychotherapeutic competence and adherence in randomly selected audio and video recordings of the sessions.

In case the intervention is terminated prematurely, an attempt will be made to continuously include the participant in the data collection. To avoid selective dropout in the control group, this group will receive an incentive. Blinding is not possible in the design of the proposed study, since both the family caregivers and the therapists will know whether a therapy is conducted. To nevertheless guarantee an independent assessment of intervention efficacy, the data collection will be performed by researchers who are not involved in the therapy.

In summary, this will be the first study to test the implementation of telephone-based cognitive-behavioral therapy in established care provision structures in a randomized controlled trial. If TEL proves to be effective in improving primary outcomes, our results will be relevant to practice. Hence, TEL could be used on a large scale. Thus, the results of the study will be used to improve support services for family-caregivers.

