**Methods/Design:**

If participants live in the area of one of the study centers (Jena, Berlin, Munich) and indicate that attendance of a face-to-face therapy is possible, they will be assigned to the face-to-face group. The other participants will be randomized to receive either telephone-based cognitive-behavioral therapy or usual care. Data will be collected at baseline, post-intervention, and at a 6-month follow-up. The primary outcomes will be depressiveness, burden of care, health complaints, and problem-solving ability. The secondary outcomes will be anxiety, quality of life, violence in caregiving, utilization of professional assistance, and cost effectiveness.

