## Methods/Design

### Design

This study is a non-blinded two-armed parallel randomized controlled trial with a third non-randomized group. Participants will be asked whether they reside in the area of a study center and can participate in the F2F. If this is the case, they will be assigned to the F2F group. If this is not the case, they will be randomly assigned to the TEL group or usual care. Random allocation will be on a 1:1 ratio basis but separated for gender and will take place after the baseline assessment. All participants will receive information materials on care and dementia. Assessments will be conducted at baseline (T0), post intervention (T1) and a 6-month follow-up (T2) (Figure 1). The TEL group will receive 12 psychotherapy sessions on the phone, whereas the F2F group will receive 12 psychotherapy sessions in direct contact in one of the participating treatment centers.

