### Procedure

Once potential participants contact the study center, they will be screened for meeting the eligibility criteria in a manual-based telephone interview. Additionally, information on the participants’ sex as well as the possibility of taking part in F2F will be assessed in this screening.

After a positive screening, all potential study participants will receive an information package including information about the study, informed consent forms for study participation and data processing as well as for telephone contact, information for the person with dementia, and several leaflets on dementia and caregiving.

For the first assessment, participants will be contacted by phone, an appointment for the telephone interview will be made for about two weeks later, and the questionnaires will be sent out. This survey technique is used because a mostly elderly study population is expected. In addition, the acceptance of the survey is to be improved and the risk of missing data or dropout to be reduced. In the telephone interview, comprehension difficulties and unanswered questions will be discussed and the questionnaires will be reviewed for completeness. After the telephone interview, the questionnaires will be returned in a return envelope.

Participants will be allocated to the three study groups after finishing the baseline assessment (T0). To ensure a sufficient number of caregivers taking part in F2F, all participants living in Berlin, Jena or Munich for whom attendance is possible will be allocated to the F2F intervention, as long as their mobility is given. A bias is not expected because the participants will not be aware of being exclusively allocated to F2F, as they will be informed about being randomized to one of the three groups. The random number generator Random.org will be used for randomization. After being informed about their group allocation, participants in the intervention groups will receive the therapy sessions. After 6 months, when the therapy is finished, the T1 assessment will be conducted. After another 6 months, the T2 assessment will be conducted. The control group will receive an allowance for participation of 40 EUR, which will be transferred after completion of the study.

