### Primary outcome measures

*Depressiveness.* A self-developed thermometer scale (0 to 100, vertical) and the Allgemeine Depressionsskala (ADS) [6] will be used to assess depressiveness. The 20 items of the ADS cover emotional, motivational, cognitive, and somatic aspects. Implementation and evaluation are standardized, Cronbach’s *α* is.89.

*Burden of care.* A self-developed thermometer scale (0 to 100, vertical) will be used to assess burden of care.

*Health complaints.* Physical health complaints will be assessed on four domains (fatigue, stomach problems, heart problems and joint pain) by using the Gießener Beschwerdebogen [7]. Besides the values of the four subscales, all 24 items can be used to calculate the subjectively experienced pressure of complaints. Regarding quality criteria, the Gießener Beschwerdebogen has standardized implementation and evaluation procedures, good internal consistency (Cronbach’s *α*.82 to.88 for the subscales and Cronbach’s *α*=.94 for the total scale) and is normed.

*Ability to solve problems relating to focused problem areas.* Problem-solving ability will be measured by Goal Attainment Scaling [8], a non-standardized manual-based instrument providing process-orientated information on how far participants are from reaching individual therapy goals. Caregivers and therapists will rate the goal attainment in the last therapy session.

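### The guarantee of independent efficacy assessment fails for one of four primary outcomes, goal attainment, and for the other three rests only on data collectors being outside the therapy

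*Protocol article*

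**What the plan says.** Under Design the article states: "This study is a non-blinded two-armed parallel randomized controlled trial with a third non-randomized group". The Discussion explains the absence of blinding by what two parties know, the family caregivers and the therapists, and then adds: "To nevertheless guarantee an independent assessment of intervention efficacy, the data collection will be performed by researchers who are not involved in the therapy".

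The abstract lists the main endpoints: "The primary outcomes will be depressiveness, burden of care, health complaints, and problem-solving ability". Under Primary outcome measures, depressiveness, burden and health complaints are measured by questionnaires and thermometer scales. Problem-solving ability has one instrument, Goal Attainment Scaling, and the section fixes who rates it and when: "Caregivers and therapists will rate the goal attainment in the last therapy session".

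Under Procedure, the paragraph on the first assessment describes questionnaires posted ahead of a telephone interview. It gives the interviewer an active part: "In the telephone interview, comprehension difficulties and unanswered questions will be discussed and the questionnaires will be reviewed for completeness". Allocation follows this assessment. For T1 and T2 the section gives the timing but not the method.

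**The concern.** The Discussion presents the use of non-therapist data collectors as what protects the efficacy assessment in a trial that cannot be blinded. Two things sit badly with that.

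First, a primary outcome is rated inside the therapy, partly by the person delivering it. A therapist's rating of goals worked on in that therapy is not independent of the treatment. Usual care offers no equivalent rater and no equivalent occasion, yet the primary objective compares TEL with usual care on this outcome.

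Second, being outside the therapy team is not the same as being unaware of the arm. The remaining primary outcomes are self-reports by caregivers who know what they received. Separation from the therapy cannot make those reports independent of allocation. Masking the interviewers would remove one avoidable route of influence, but the article does not say whether this is done.

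At stake is how a TEL benefit would be read. Someone relying on the guarantee would think the primary results better protected against assessment bias than the described procedures make them.

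**Working it through.** No figure in the plan depends on this point and the correction changes none, so the check is a comparison of statements.

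**Step 1: which primary outcomes meet the stated property.** The property is that "the data collection will be performed by researchers who are not involved in the therapy".

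| Primary outcome | Instrument | Rated by | Collected outside the therapy? |
|---|---|---|---|
| Depressiveness | ADS and thermometer scale | Caregiver | Yes, by the Discussion |
| Burden of care | Thermometer scale | Caregiver | Yes, by the Discussion |
| Health complaints | Gießener Beschwerdebogen | Caregiver | Yes, by the Discussion |
| Problem-solving ability | Goal Attainment Scaling | Caregiver and therapist | No, rated in session |

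The property fails for 1 of 4. The raters in the last row cannot be the independent therapists mentioned later in the Discussion. Those judge competence and adherence from recordings, not goal attainment.

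**Step 2: whether the goal rating exists in both randomized arms.** The rating is tied to the last therapy session. Usual care has no therapy sessions, so no rating occasion is described there. The goals themselves are identified in the problem-analysis module of the intervention, and the article describes no goal setting for usual care. As written, the outcome has no described counterpart in the comparator arm.

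**Step 3: whether the reason for not blinding covers the interviewers.** The Discussion's reason names caregivers and therapists. Data collectors are a third party, and nothing in that reason requires them to know the arm. No masking of them is stated and no reason for leaving them unmasked is given.

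**Step 4: whether interviewers could influence answers after allocation.** The telephone review is described for the first assessment. Allocation comes after T0, so at that point there is no arm to favour. Influence is possible only if the same review is used at T1 and T2. The article does not say that it is. Its rationale (a mostly elderly sample, fewer missing data and dropouts) would apply there equally, so reuse is plausible but remains an assumption.

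**The case against.** The best defence is that independent does not mean blinded. The article discloses the lack of blinding twice, under Design and in the Discussion, and the disputed sentence can be read as promising only separation from treatment delivery. That stands. It also shows why the sentence should not speak of a guarantee, since separation does little for self-reports by unblinded caregivers.

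It can also be said that the sentence covers only the T0, T1 and T2 surveys, with goal attainment handled apart. The sentence is not so limited: it speaks of assessing efficacy, and goal attainment is the sole measure of a primary efficacy outcome.

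A third defence is that this is a condensed article and interviewer procedures may sit in the full protocol. That stands for masking, where the text is merely silent. It does not help with the goal rating, where two published statements conflict.

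Several stronger readings are tempting but not supported:

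- **The interviewers are known to be unmasked.** The article says neither that they are nor that they are not. The word non-blinded is explained only by reference to caregivers and therapists.
- **Interviewer help will bias T1 and T2.** That help is described only before allocation, and it concerns comprehension, unanswered items and completeness, not scoring.
- **The therapist alone scores a primary outcome.** The caregiver rates too. This softens the point without removing it, because both ratings are made in session.
- **The bias can be sized.** Assuming a shift of 0.05 to 0.10 SD and dividing by the plan's expected effects gives 0.05/0.41 = 12% and 0.10/0.41 = 24% at the upper end, and 0.05/0.14 = 36% and 0.10/0.14 = 71% at the lower end. The assumed shift has no source in the document, so these percentages are not evidence of any bias.

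**Conclusion.** The point holds in two parts of unequal strength.

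The firm part is a contradiction. The Discussion's guarantee is untrue for 1 of the 4 primary outcomes, because goal attainment is rated within the therapy, in part by the therapist, on an occasion that one of the two randomized arms does not have. This rests on the text alone, apart from taking the therapist in the last session to be the treating one, which is the natural reading.

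The weaker part is that, for the other three primary outcomes, the only named safeguard falls short of masking and the stated reason for not blinding does not reach the interviewers. Whether this matters depends on two things the article leaves open: whether T1 and T2 interviewers know the allocation, and whether they review answers by telephone as at T0. The size of any effect is unknown. The main exposure, self-report by caregivers who know their arm, would remain even with masked interviewers.

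**What to change.** 1. **Reconcile the Discussion with Primary outcome measures.** Use the caregiver's goal-attainment rating, collected by the non-therapist researchers at T1 in both randomized arms, as the primary measure of problem-solving ability. Report the therapist's rating as process information only. The caregiver's rating then carries the outcome, so it is not left without a measure. This works only if usual-care participants have recorded goals. If they have none to rate, goal attainment should not be a primary TEL versus usual-care outcome, and the primary objective and the multiplicity correction should be rewritten to match.
2. **Protect the T1 and T2 interviews.** Assign them to existing researchers without access to the allocation list, script the help they may give on items, and record any unmasking.
3. **Reword the Discussion.** Replace the guarantee with a statement that the outcomes are unblinded self-reports collected by researchers outside the therapy.

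The cost is a reassignment of interviews, a short script, and moving one caregiver rating from the last session to the T1 assessment. That no extra staff are needed is an assumption, since the article gives neither the number of researchers nor who handles allocation. Two downsides remain: some interviewers will be unmasked by what participants say, and the therapist's rating no longer counts as primary evidence.
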